### Objectives

This study has three main objectives. First, test the safety of tSCS applied below the level of injury to the lumbosacral spinal cord after acute spinal cord injury, starting 72 h after injury. We hypothesize that there will be no adverse events associated with acute application of tSCS. Second, demonstrate the proof-of-principle that tSCS application in the acute phase post-injury can potentiate recovery. We hypothesize that tSCS can improve volitional movement and/or sensation acutely after SCI as measured by an improved lower extremity motor score in the presence of tSCS. Third, identify treatment-related mechanistic biomarkers (exploratory). We hypothesize that there will be fluid-based biomarkers that will change in the setting of tSCS receipt.

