### Intervention and comparator

Transcutaneous spinal stimulation will be delivered using ARC^EX^ device (ONWARD Medical), via skin surface electrodes placed over the spine targeting lumbosacral spinal cord at T10 and L1 using round 3.2 cm in diameter stimulating electrodes, and bilaterally on the iliac crests using rectangular, 7.5 × 13 cm reference electrodes during the intervention. Based on previous studies on safety and efficacy of tSCS, we will use biphasic waveforms with a burst frequency of 30 Hz, a carrier frequency of 10 kHz, with a pulse width of 1,000 μs (Gerasimenko et al., 2015; Keller et al., 2021; Moritz et al., 2024). Stimulation will be delivered continuously for 60 min once (for Phase 1 participants) and once a day for 5 consecutive days (for Phase 2 participants). The intensity of the stimulation will be increased gradually to the motor threshold intensity (Moritz et al., 2024) and lowered until motor responses subside if there are any. Increase in trunk/lower extremity muscle tone will be additionally monitored to assess whether the amplitude of stimulation required to reach motor threshold changes with days post injury + tSCS treatment for Phase 2 participants. If stimulation does not elicit any obvious motor responses due to spinal shock, the stimulation intensity will be chosen based on previously reported ranges of effective stimulation, including those observed in our ongoing clinical trial in patients with chronic low back pain (NCT05265000) which provides ranges of maximum tolerable stimulation intensities in individuals without SCI, who have full sensation. The stimulation parameters used in that study are identical to those proposed in STEP-RAISE, including waveform, pulse width, carrier frequency, and electrode configuration, allowing for adaptation of stimulation intensities if necessary. The specific stimulation parameters and optimal stimulation intensity will be left to the discretion of the investigators during this experimental treatment. A range of the investigated stimulation parameters will be systematically recorded and will be reported as part of the methodology for each participant. The stimulation will be delivered while the participant is lying supine in the ICU bed. The lower motor ISNCSCI exam will be performed within the last 30 min of stimulation to assess whether acute tSCS potentiates volitional lower extremity movement. Although physical therapy (PT) is provided to acute SCI patients, in this trial the goal is to assess whether tSCS alone can be delivered safely, and will not be combined with the standard of care ICU PT. Participants will be continuously monitored and asked to provide any verbal feedback regarding stimulation to ensure there is no pain or discomfort during treatment.

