### Outcomes

Table 1 lists all trial outcome measures and the corresponding abbreviated statistical analysis plan.

**Table 1 tab1:** A list of outcome measures and the corresponding analysis plan.

Outcome measure	Description	Statistical analysis
Primary outcomes (safety)—Phase 1 and 2		
1. Incidence of adverse events (# of observed events/sessions)	Hemodynamic instability Skin irritation Patient condition deterioration Unanticipated adverse events	Data type: Count Data Statistical Test: Fisher’s Exact Test
Primary outcomes (efficacy)—Phase 2		
1. ISNCSCI lower motor scores	Immediate change in scores with acute tSCS Change in scores from baseline to post tSCS	Data Type: Integer Statistical Test: Repeated Measures Analysis of Variance
Secondary outcomes (efficacy)—Phase 1 and 2		
1 ISNCSCI sensory + motor scores	Change in scores from baseline to 7DPI or discharge	Data Type: Integer Statistical Test: Repeated Measures Analysis of Variance
2. Spinally motor evoked potentials (MEPs)	MEP present/elicited (binary measure) (within subject) # of muscles with elicitable MEP	Data Type(s): Binary, Count Statistical Tests: Chi-Square, Fisher’s Exact Test
3. Electromyography (EMG) amplitude	Change in EMG amplitude in the presence of tSCS vs. no stimulation (within subject) Change in number of muscles with EMG output	Data Type(s): Continuous, Count Statistical Tests: Repeated Measures Analysis of Variance, Fisher’s Exact Test
Secondary outcomes (biomarker discovery)—Phase 1 and 2		
1. Neuronal (UCH-L1) and glial cell (GFAP) injury markers in blood	Changes in protein levels from baseline to post tSCS vs. sham	Data Type: Continuous Statistical Tests: Repeated Measures Analysis of Variance
2. CSF proteomics	Changes in protein levels from baseline to post tSCS vs. sham	Data Type: Continuous Statistical Tests: Non-linear Principal Components Analysis, followed by RM-ANOVA on PC scores
Secondary outcomes (patient-reported outcomes)—Phase 1 and 2		
3a. Incidence of neuropathic pain at 6-month follow-up 3b. Severity of neuropathic pain at 6-months follow-up	Modified DN4 questionnaire will be used to assess neuropathic pain at 6-months follow-up in tSCS vs. sham individuals (vs. historical TRACK-SCI participants)	Data Type: Integer, or Binarized at ≤ indicating neuropathic pain Statistical Test: Independent group Student’s *t*-test, or Chi-square

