### Data collection methods

Once consent is obtained, coordinators will record all clinical variables and medical history in a secure, web-based portal (REDCap) in NINDS SCI Common Data Elements format. Within 72–96 h post-injury, patients will undergo baseline assessments including pain questionnaires [DN4 and International Spinal Cord Injury Pain Data Set (ISCIPDS)], International Standards for Neurological Classification of SCI (ISNCSCI) with electromyography (EMG), blood and CSF (if a lumbar drain is already in place for clinical purposes only) sampling for biomarkers. We anticipate that most, if not all, eligible subjects will have a lumbar drain as it is part of standard of care at our institution. Lower motor ISNCSCI will be repeated during the last 30 min of tSCS and at 7 days post-SCI (or at hospital discharge whichever is earlier). Surface EMG recordings obtained during active tSCS may contain stimulation-related artifacts. Appropriate signal processing procedures will be applied prior to analysis to reduce stimulation artifacts as necessary (Kim et al., 2021). Residual artifact contamination will be considered during interpretation of EMG findings.

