### Analysis of primary and secondary efficacy outcome measures

For all participants, the primary outcome measure(s) will be: incidence of adverse events (number) for Phase 1 and 2 and change in ISNCSCI lower motor score over time for Phase 2. Secondary outcomes in both phases will be: ISNCSCI sensory scores, AIS grade, peak EMG amplitude, and mean EMG amplitude. For Phase I, change scores will be measured between baseline and post-trial, and in Phase II each measure will be taken across 5 trials. For all repeated measures analyses, we will use a factorial within-subjects repeated-measures analysis of variance (RM-ANOVA) to assess statistically significant change over time. This approach will allow us within a single statistical test to assess (1) the overall between-subjects effect of stimulation to determine the group differences between the stimulation and control groups, (2) the difference in changes over time between groups, and (3) the within-subjects effect of stimulation over trials, to determine the extent to which each individual changes over time. The RM-ANOVA procedure will be run for each outcome measure.

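### The on-versus-off EMG amplitude outcome cannot separate voluntary output from residual stimulation artifact or evoked muscle activity, both of which can occur only in active recordings

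*Protocol article*

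**What the plan says.** Table 1 (Outcomes) lists EMG amplitude as a secondary efficacy outcome for both phases, described as "Change in EMG amplitude in the presence of tSCS vs. no stimulation (within subject", together with a change in the number of muscles showing EMG output. The tests named are "Statistical Tests: Repeated Measures Analysis of Variance, Fisher’s Exact Test". The section on analysis of primary and secondary efficacy outcome measures specifies "peak EMG amplitude, and mean EMG amplitude". It runs the same ANOVA on every outcome, to test the within-subject change and also "the overall between-subjects effect of stimulation to determine the group differences between the stimulation and control groups".

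Under Intervention and comparator, sham participants wear the electrodes but receive no current. For active participants, "The intensity of the stimulation will be increased gradually to the motor threshold intensity", and is then reduced until any motor response stops. If spinal shock means no obvious response is seen, intensity is taken from ranges reported elsewhere. The same section says that the leg motor examination during stimulation is meant to show whether tSCS enhances voluntary leg movement.

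Data collection methods acknowledges that recordings under active tSCS may contain artifact and plans signal processing before analysis where needed. It adds: "Residual artifact contamination will be considered during interpretation of EMG findings".

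**The concern.** The contrast compares two recording conditions that differ in more than voluntary effort. With current on, surface EMG can contain voluntary activity, leftover stimulation artifact and muscle activity driven by the current itself. With current off, or under sham, only the first is possible. The two extra components add to the recorded amplitude in the same direction as the hoped-for benefit. Sham cannot cancel them because it never produces them, and Phase 1 has no sham arm.

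If the on-stimulation contrast is read as evidence about voluntary output, part or all of an apparent gain could be the stimulation itself. The Sample size section intends efficacy outcomes to supply effect sizes for later trials, so a bias in one direction could carry forward.

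**Working it through.** The article states no EMG mean, SD, artifact size or EMG-based power, so there is no planned figure to reproduce. The check has three parts.

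**1. What the contrast measures.** Let V be voluntary activity, A residual artifact, E evoked activity and N noise, as independent components measured as RMS (an assumption), so that their squares add.

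- Active, current on: V_on² + A² + E² + N²
- Active, current off: V_off² + N²
- Sham, both states: V² + N²

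If voluntary output does not change, the on-minus-off difference is A² + E² in the active arm and 0 under sham. The between-arm difference is then also A² + E². Processing shrinks A. Lowering intensity from threshold shrinks E. Neither step is described as bringing its term to zero, and artifact removal does not act on E, which is genuine muscle signal.

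**2. What a leftover shift would do to the tests.** Inputs: 5 active and 5 sham participants (Trial design) and alpha 0.05 (Sample size; two-sided assumed). The true volitional effect is set to zero. The shift b, in SDs of the on-minus-off change, is assumed to be present only under active current. One change per participant is used as a simplification of the planned ANOVA. Rejection probabilities come from the noncentral t distribution:

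- active versus sham: noncentrality b·√(5/2), 8 df
- within active, n = 5: b·√5, 4 df
- within active with the five Phase 1 participants added, n = 10: b·√10, 9 df (pooling is an assumption)

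| b (assumed) | 5 vs 5 | within, n = 5 | within, n = 10 |
|---|---|---|---|
| 0 | 5.0% | 5.0% | 5.0% |
| 0.25 | 6.4% | 7.2% | 10.9% |
| 0.5 | 10.8% | 14.1% | 29.3% |
| 1 | 28.6% | 40.1% | 80.3% |
| 2 | 79.1% | 90.9% | >99% |

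The documents do not show which row applies. If processing and titration work well, the trial sits near the top of the table.

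**3. How a resting reference should be subtracted.** Take assumed values of V = 5 and contamination C = 10 (microvolts RMS, noise ignored). The attempt reads √(5² + 10²) = √125 = 11.2, and rest in the same state reads 10.

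- Linear subtraction: 11.2 − 10 = 1.2, against a true 5, which would bias against active.
- Squared subtraction: √(125 − 100) = √25 = 5, which recovers the true value.

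**The case against.** The plan is not naive about this. It names artifact, processes it before analysis and says the remainder will be weighed. It also lowers intensity until motor responses stop, which directly limits evoked activity, and the spinal-shock exception applies when no response is obvious. Filter settings and rest-trial procedures may well be in a fuller document, so their absence from an article is not a fault in itself. With small contamination the effect is trivial: 1 microvolt on 5 gives √26 = 5.1, a 1.02-fold rise.

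A reader might infer that the evidence for the second objective is itself biased. The documents do not support that. Objectives states the hypothesis that "tSCS can improve volitional movement and/or sensation acutely after SCI" but ties it to the lower extremity motor score, not to EMG. Table 1 labels this outcome EMG amplitude; the volitional reading comes from the purpose given for the on-stimulation motor examination. The muscle-count line does not say in which stimulation state the count is taken. The outcome is secondary, and the Sample size section calls efficacy analyses exploratory.

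These points limit the consequence but do not remove the problem. Weighing artifact at interpretation leaves it in the ANOVA, and in any muscle count made with current on. Surface EMG can register activity that is not obvious to an observer. The defined contrast is itself on versus off, which is a choice the article makes and not a detail deferred elsewhere.

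**Conclusion.** The point holds as a weakness in how a secondary, exploratory outcome is defined. Residual artifact and evoked activity can arise only with current on, and they align with the treatment effect both within subjects and between arms, so they could be mistaken for voluntary gain. This rests on sham delivering no current and on the contrast as worded in Table 1.

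The size is unknown. The rejection rates above depend on assumed shifts and show sensitivity, not an expected error rate. A reader might also infer that contamination will be counted as improved voluntary output, or that a participant with no voluntary function will show a large increase. The text supports only that this could happen, given the planned processing and titration. The change is worth making before recording starts, because a stimulation-on resting reference cannot be recovered afterwards.

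**What to change.** In Table 1, Data collection methods and the efficacy analysis section:

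- Record a brief no-effort interval in the same stimulation state as each attempted contraction: on-stimulation rest for on-stimulation attempts, off-stimulation rest for off-stimulation attempts.
- Define volitional EMG relative to that rest, subtracting in squared RMS amplitude (power), not linearly. This does not carry over to peak amplitude, which is better kept descriptive.
- Count a muscle as active only if the attempt exceeds its same-state rest.
- Put active and sham recordings through the same processing pipeline, so that any effect of the filter on genuine EMG is shared by both arms.
- Base any claim of volitional gain on the stimulation-off contrast, baseline versus post-treatment or 6 months, with the on-stimulation contrast as supportive. EMG is already planned with the baseline and 6-month examinations.

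None of this changes stimulation settings. The cost is a few seconds of extra recording per attempt and somewhat noisier estimates, some of which may fall below zero on the power scale. The stimulation-off contrast also answers a different question: it shows change that persists without current, not the immediate effect. The on-stimulation result should therefore still be reported, with that limit stated.

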### Harms

Potential harms associated with study participation include risks related to tSCS, biospecimen collection, and data privacy. Adverse events related to tSCS may include autonomic changes such as autonomic dysreflexia, manifested by blood pressure fluctuations, sweating, or headache, as well as skin irritation at electrode sites. Autonomic dysreflexia is less common in the acute phase of SCI but will be monitored closely. Although electrical stimulation in the acute phase of SCI could theoretically impair neurological recovery, this has not been observed in prior studies of chronic SCI. Risks associated with blood collection include transient pain, bruising, redness or swelling at the venipuncture site, infection, and rare episodes of fainting; blood will be drawn from existing intravenous lines whenever possible to minimize these risks. Cerebrospinal fluid sampling will be performed via an existing lumbar drain, accessing the drain carries a potential risk of infection, which will be mitigated through sterile technique. Risks related to privacy and confidentiality will be minimized through de-identification of data and biospecimens and secure storage procedures. Harms will be assessed systematically throughout the trial. Participants will be continuously monitored in the Neurointensive Care Unit, where neurological, cardiovascular, hematopoietic, abdominal, pulmonary, infectious, wound-related, and laboratory complications are routinely assessed as part of standard clinical care for acute spinal cord injury. Continuous telemetry and neurological examinations will be performed per standard of care. Vital signs will be recorded during tSCS sessions, along with surface electromyography recordings. The study team will document all vital signs and any vasoactive medications or infusions administered during stimulation sessions. All adverse events will be recorded by the study team and reviewed by the PI and the safety monitor. Events will be categorized by severity (mild, moderate, or severe) and assessed for their relationship to study participation (unrelated, possibly related, probably related, or definitely related). Serious adverse events and unanticipated adverse device effects will be reported in accordance with UCSF Institutional Review Board and sponsor requirements. Predefined stopping criteria include clinically significant hemodynamic instability, autonomic dysreflexia, deterioration in clinical status, and any serious adverse event judged to be related to the intervention.

### Participant timeline

Time schedule of enrollment, interventions, assessments, and visits for participants is shown in Figure 1.

### Sample size

Because no prior studies have evaluated tSCS during the acute phase of SCI to our knowledge, there are currently no directly comparable data available to support a conventional efficacy-based sample size calculation. Therefore, sample size estimates were informed by published studies in chronic SCI populations that employed similar stimulation paradigms and outcome measures. Power calculations on our preliminary patient data in children (*N* = 8) and adults (*N* = 15) (Sayenko et al., 2019) with chronic SCI suggest that the factorial within-subjects design yields sufficient power (1 − *β* > 0.80) to detect significant main effects of stimulation. Independent repeated-measures analysis of a recently published high-profile study (Moritz et al., 2024) that employed a similar transcutaneous stimulation paradigm (*N* = 60 participants) revealed that stimulation significantly improved ISNCSCI outcome measures over time (*p* < 0.05) with medium to large effect sizes and very high observed power (sensory score, eta squared effect size = 0.08, observed power = 1.0; motor score, eta squared effect size = 0.18, observed power = 0.97). To detect a difference with effect sizes as strong or stronger than seen in these analyses, with a power of 1 − *β* = 0.80 and alpha level set to 0.05. Although these effect sizes may not directly translate to the acute SCI setting, they provide a preliminary basis for study planning in the absence of acute SCI data. We will aim to enroll 15 subjects (*n* = 5 for Phase 1, and *n* = 10 for Phase 2). Given the expected heterogeneity of acute SCI and the small sample size, the study is not powered to detect modest between-group differences and efficacy analyses should be considered exploratory. Consistent with the early-phase safety and feasibility objectives of the study, efficacy outcomes will be used to estimate variability and effect sizes to inform future adequately powered clinical trials.

### Recruitment

We will prospectively identify potential subjects and enroll individuals presenting with ASIA A-C aSCI at ZSFG. Clinical research coordinators with formal training will begin screening patients upon admission to the emergency department and intensive care unit. We anticipate our sample size is feasible as ZSFG admits an average of 3–4 aSCI patients each month. Once a patient is confirmed to meet inclusion criteria, they will be approached for informed consent. Capacity to provide informed consent will be assessed prior to enrollment by experienced research study staff/physicians. Individuals with impaired decision-making capacity due to sedation, cognitive impairment, or acute medical illness will not be enrolled until the capacity is restored.

### Randomization

In Phase 2, subjects will be randomized to active or sham tSCS treatments using simple randomization, in a 1:1 ratio. The random allocation sequence will be generated by an independent study statistician using a computer-based randomization algorithm. Allocation concealment will be ensured using a centralized, computer-based randomization system accessible only at the time of assignment, thereby preventing foreknowledge of treatment allocation. Clinical research coordinators will enroll participants, and the treatment assignment will be implemented by a designated unblinded investigator responsible for administering the intervention. Baseline injury characteristics, including AIS grade, neurological level of injury, ISNCSCI scores, and MRI/BASIC score when available, will be summarized by treatment group and considered when interpreting preliminary efficacy outcomes.

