### Trial design

We will conduct a Phase 1 and Phase 2 clinical trial (Figure 1). Phase 1 is an open label study focused on determining safety of the initial 60 min of tSCS between 72 and 96 h after spinal cord injury (*n* = 5). Phase 2 is a randomized, placebo-controlled triple-blinded clinical trial with a parallel group assignment (active tSCS, *n* = 5 and sham tSCS *n* = 5) focused on determining safety and efficacy of tSCS for treatment of acute SCI. A total of 15 subjects will be enrolled across Phase 1 and Phase 2. A sham-controlled design was selected to isolate the physiological effects of electrical stimulation from nonspecific influences related to device application, participant expectations, investigator interaction, and increased clinical monitoring.

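### Simple randomization of 10 Phase 2 participants gives the stated 5 active and 5 sham only about one time in four, and leaves AIS balance to chance

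*Protocol article*

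**What the plan says.** The Trial design section describes a "parallel group assignment (active tSCS, *n* = 5 and sham tSCS *n* = 5", and the Sample size section agrees on the total: "We will aim to enroll 15 subjects (*n* = 5 for Phase 1, and *n* = 10 for Phase 2". The Randomization section then states that "subjects will be randomized to active or sham tSCS treatments using simple randomization, in a 1:1 ratio". It describes a computer-generated sequence from an independent statistician, central concealment, enrolment by coordinators, and assignment carried out by an unblinded investigator who gives the treatment. It names no block, stratum, minimization factor or fixed list.

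On severity, AIS grades A, B and C are all eligible; the Recruitment section plans to "enroll individuals presenting with ASIA A-C aSCI at ZSFG". AIS grade, neurological level, ISNCSCI scores and the MRI score (when available) "will be summarized by treatment group and considered when interpreting preliminary efficacy outcomes". The repeated-measures ANOVA in the efficacy analysis section is to assess "the overall between-subjects effect of stimulation to determine the group differences between the stimulation and control groups", among other effects. That section names no severity term.

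**The concern.** The design section states a fixed split, and the allocation method does not produce one. Under simple randomization each participant is allocated independently, so 5 per arm is only the average over hypothetical repetitions. Both statements are current text, and the method itself is stated, so this is not a detail left to an unseen document.

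Two things are at stake. One is precision of the between-group comparison, which falls as the arms become unequal. The other is safety exposure. Adverse events are a primary outcome in both phases, and Phase 2 is the only source of data on five daily active sessions, so a small active arm would reduce what the trial learns about repeated stimulation.

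The primary efficacy outcome in Phase 2 is the lower motor score, and participants range from AIS A to C. Nothing in the allocation steers the grades toward balance.

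**Working it through.** **Inputs.** Phase 2 total 10 and stated arms 5 and 5 (Trial design, Sample size); independent allocation with probability 0.5 (Randomization). The documents give no AIS mix, so the AIS figures in steps 4 and 5 rest on assumed mixes.

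**1. The plan's own figure.** The expected number per arm is 10 × 0.5 = 5. The stated 5 and 5 is reproduced as an expectation only.

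**2. Realised split.** The number allocated to active is Binomial(10, 0.5), so P(k active) = C(10, k)/1024. Variance of the arm difference relative to 5:5 is (1/n1 + 1/n2)/(1/5 + 1/5); the standard error ratio is its square root.

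| Split (either way) | Probability | Relative variance | Relative SE |
|---|---|---|---|
| 5:5 | 252/1024 = 24.6% | 1.00 | 1.00 |
| 6:4 | 420/1024 = 41.0% | 1.04 | 1.02 |
| 7:3 | 240/1024 = 23.4% | 1.19 | 1.09 |
| 8:2 | 90/1024 = 8.8% | 1.56 | 1.25 |
| 9:1 or 10:0 | 22/1024 = 2.1% | 2.78 at 9:1 | 1.67 at 9:1 |

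Hence P(not 5:5) = 75.4%, P(7:3 or worse) = 352/1024 = 34.4%, and P(8:2 or worse) = 112/1024 = 10.9%.

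**3. Safety exposure.** P(3 or fewer active) = (1 + 10 + 45 + 120)/1024 = 176/1024 = 17.2%. If no active participant has an event, the one-sided 95% upper bound on the participant event rate is 1 − 0.05^(1/n): 45% with n = 5, 63% with n = 3, 78% with n = 2.

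**4. AIS grade under two schemes.** Take k AIS C participants among the 10 (assumption: k = 2 or 3). The probability that all fall in one arm is:
- simple randomization: 2 × 0.5^k = 50% (k = 2), 25% (k = 3);
- list fixed at five and five: 2 × C(10 − k, 5 − k)/252 = 2 × 56/252 = 44% (k = 2), 2 × 21/252 = 17% (k = 3).

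Fixing the arm sizes therefore does little for AIS balance.

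**5. Stratified blocks, checked as an alternative.** Take two AIS strata.
- Blocks of 2, both strata odd-sized (3 and 7, or 5 and 5): each stratum ends one participant out of balance, in a random direction. The result is 5:5 with probability 50% and 6:4 with probability 50%.
- Blocks of 2 and 4 in random order, the two sizes equally likely (assumption), strata of 2 and 8. In the small stratum, both participants land in one arm with probability 1/2 × 1/3 = 16.7%. In the large stratum, the last block is an incomplete block of 4 with probability 0.3125, and it then ends two participants out of balance with probability 1/3, giving 0.3125/3 = 10.4%.
  - 5:5 needs both strata balanced or opposite imbalances: 0.833 × 0.896 + 0.167 × 0.104 × 0.5 = 75.5%.
  - 7:3 needs both imbalances in the same direction: 0.167 × 0.104 × 0.5 = 0.9%.

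Stratified blocking improves AIS balance but does not guarantee 5:5.

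**The case against.** The strongest reply is that little is lost. The Sample size section says the trial is not powered for modest between-group differences and calls the efficacy analyses exploratory. A 6:4 split costs 4% in variance and a 7:3 split about 9% in standard error. Five Phase 1 participants receive active stimulation whatever happens in Phase 2, though for one session only. All of this stands, and it limits the severity. It does not remove the conflict between the two sections, and the estimates of variability and effect size that the trial is meant to supply are the quantities that unequal arms make less precise.

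A second reply is that simple may have been used loosely to mean unstratified, with a constrained list intended. That is possible. The text as written still describes unrestricted allocation and would need correcting.

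A third is that unpredictability is a legitimate reason to prefer simple randomization. One role is unblinded by design and sees every past assignment, so any restriction makes some later assignments inferable to that person without a breach of the blind. This stands as a real cost of the fix.

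A reader might infer that the method leaves AIS grade unbalanced and makes the lower motor score comparison uninterpretable. The documents do not support that. Balance is left to chance, the AIS mix is not given, and no passage ranks AIS grade as the main prognostic factor or sets a cut between grades. The outcome is a change from baseline plus an immediate change with stimulation, and the ANOVA includes within-subject effects, so differences in starting level are partly removed. Different natural recovery by grade is not removed.

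**Conclusion.** The point holds as an inconsistency between the Trial design and Randomization sections. The stated 5:5 has probability 24.6%; 7:3 or worse has 34.4% and 8:2 or worse 10.9%. These figures are exact and assume only 10 randomized participants and independent 1:1 allocation, which is what the text describes. AIS balance is left to chance, and how often it fails depends on an assumed mix.

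This should be fixed, ideally before the first Phase 2 allocation. It is not essential to the trial's validity, given the exploratory status of efficacy and the small loss at the most likely split, 6:4. A reader might also infer that stratified blocking by AIS is required, or would settle both problems. It is optional, and it would not secure the stated arm sizes.

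**What to change.** In the Randomization section, replace simple randomization with a concealed, randomly ordered list of exactly five active and five sham assignments, held in the centralized system already planned. That raises the probability of 5:5 from 24.6% to 100% when ten people are randomized. It takes one sentence and a new list from the study statistician.

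The downside is that once one arm is full, the remaining assignments are known to the unblinded treating investigator. The section should therefore state that this person has no part in screening or enrollment, and that the coordinators who enrol do not see past assignments.

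The section should also acknowledge that the list does not balance AIS grade. If the sponsor prefers to stratify by AIS, the plan should say that the final split can be 6:4 or slightly worse, and the Trial design section should then give 5 and 5 as a target.
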